**3.5 Post refractive surgery controls**

Flap creation methods：

1. One-Use Plus SBK Moria microkeratome (Moria, Antony, France);
2. IntraLase Femtosecond Laser (Abbott Medical Optics, Santa Ana, CA, USA).

Pre operation medication：

(1) Levofloxacin

(2) Artificial tears (one of three)

Sodium carboxymethylcellulose

Dextran hydroxypropyl methyl cellulose

Polyvinyl Alcohol

Post operation medication：

(1) Levofloxacin

(2) Artificial tears (one of three)

Sodium carboxymethylcellulose

Dextran hydroxypropyl methyl cellulose

Polyvinyl Alcohol

(3) Fluorometholone Acetate

Notice: Keep records if temporarily adjust the medication.

**3.6 Data analysis:**

All data were collect and save in Excel to build a database.

Statistical methods were used to analysis data.

1. T-test；
2. Liner Regression, Pearson’s correlation.

4 Subjects information

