**1.2 Aims**

A. Using OCT to obtain corneal images before LASIK, post LASIK 1 day, 1 week, 2 weeks, 1 month. Compare the differences between two flap creation methods.

B. Observe the cornea images acquired from keratoconus patients in different stages. Analysis thickness data and the relationship between the thickness and stage.

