**2.2 Ultra-high resolution OCT (UHR-OCT)**

Custom-built UHR-OCT equippmented with superluminescent diode light source (SLD) with a wavelength centered at 840 nm and band width of 100 nm. The output power is less than 1.30 mW as safety limit (ANSI Z136.1). The scan depth is 2.0 mm in the air with scan speed of 24000 A-line/sec. The axial resolution was ~3.0μm and lateral resolution was ~15μm. This instrument capture images at horizontal and vertical directions. Real-time image in two directions might help to relocation on the corneal vertex. OCT probe was fixed on the slit lamp and easy to adjust the imaging capture positions.

UHR-OCT is used to obtain 3 dimensional corneal images for corneal epithelium, Bowman’s layer and corneal flaps.

**2.3 Lab conditions**：dim light, temperature 1.5-25oC，humidity 30-50%.

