**3.3.2 Formal study**

**（1）visiting spots：**Pre, post 1 day, 1week, 2 weeks, 1month, 3months.

**（2）OCT scanning：**according torandom number table, select one eye.

**A. UL-OCT：**run: C:\OCT\combined_x-y\OCT-T34-Combined_1.vi

1.Obtain OCT images as following：

**1）Central 3D radial scanning：**calibrated scan width 18.291mm.Scanning setting：“X/Y scan width” set as 15, “line rate” set as 24000 k/A-line，“scan pattern” set as 2048×324 mm radial.

[figure not shown]

**2）Horizontal 2D scanning：**calibrated scan width 12.139 mm. Scanning setting：“X/Y scan width” set as 10, “line rate” set as 24000 k/A-line，“scan pattern” set as 2048×324 mm.

[figure not shown]

**3）Vertical 2D scanning：**calibrated scan width 12. 248 mm. Scanning setting：“X/Y scan width” set as 10, “line rate” set as 24000 k/A-line，“scan pattern” set as 2048×324 mm.

[figure not shown]

**2. Naming rules：** NO1_XX_S_1M_OD_2D_X10_1

**3. Data saving：** E:\LASIK_OCT\UL\Time\Subject

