**4. Notice：**

(1) Using apex to adjust cornea vertex registration and relocation;

(2) Keep iris plane balanced;

(3) Check the image quality after each acquisition. Reacquire if the image quality is not good enough.

(4) Open the eyelid wide to avoid eye lash artifacts.

(5) Check 3D scanning image quality. Require if the reconstruction is not smooth.

**B． UHR-OCT：**run: C:\OCT\combined_x-y\OCT-T34-Combined_1.vi

1. Obtain OCT images as following：

**1）Central horizontal 2D scanning：**calibrated scan width 8.425 mm. Scanning setting：“X/Y scan width” set as 7, “line rate” set as 24000 k/A-line，“scan pattern” set as 2048×326 mm.

[figure not shown]

**2）Nasal horizontal 2D scanning：**calibrated scan width 8.425 mm. Scanning setting as “1）Central horizontal 2D scanning”.

**3）Temporal horizontal 2D scanning:** calibrated scan width 8.425 mm. Scanning setting as “1）Central horizontal 2D scanning”.

**4）Central vertical 2D scanning：**calibrated scan width 8.418 mm. Scanning setting：“X/Y scan width” set as 7, “line rate” set as 24000 k/A-line，“scan pattern” set as 2048×326 mm.

[figure not shown]

**5）Superior vertical 2D scanning：**calibrated scan width 8.418 mm. Scanning setting as “1）Central vertical 2D scanning”.

**6）Inferior vertical 2D scanning：**calibrated scan width 8.418 mm. Scanning setting as “1）Central vertical 2D scanning”.

**7）Central 3D radial scanning：**calibrated scan width 8.418 mm. Scanning setting：“X/Y scan width” set as 10.5, “line rate” set as 24000 k/A-line，“scan pattern” set as 2048×324 mm radial.

[figure not shown]

**2. Naming rules：** NO1_XX_S_1M_OD_N_2D_X10_1

**3. Data saving:**  E:\LASIK_OCT\UHR\Time\Subject

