**3.4 OCT imaging processing:**

UL-OCT: using custom developed automated software to reconstruct cornea.

UHR-OCT: using custom developed automated software to obtain thicknesses of each corneal sublayers.

Imaging processing: (1) raw images; (2) manual measurements (J-OCT): interfaces and boundaries of each sublayer; (3) automated Matlab code: detailed measurement results of all corneal layers.

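### Section 3.6 lists only t-test, linear regression and Pearson's correlation for a design with six visits per eye; none, as listed, models repeated measures or tests whether the time course differs by flap method

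*Protocol*

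**What the plan says.** All references are to the protocol; a separate SAP, if one exists, was not available.

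- **Methods.** Section 3.6 (Data analysis) has two numbered items: the t-test, and "Liner Regression, Pearson’s correlation". It does not say whether t-tests are paired, whether visits are analysed one by one or together, or which method serves which aim.
- **Visits.** Section 3.3.2 schedules six: "Pre, post 1 day, 1week, 2 weeks, 1month, 3months". Aim A in section 1.2 names five: "before LASIK, post LASIK 1 day, 1 week, 2 weeks, 1 month".
- **Comparison.** Aim A is to "Compare the differences between two flap creation methods" using images from those visits. Section 1.3 expects oedema to recede with time after surgery, and plans to correlate refractive regression, curvature and oedema.
- **Outcomes.** UHR-OCT is used for "corneal epithelium, Bowman’s layer and corneal flaps" (section 2.2), with automated processing of every sublayer: "using custom developed automated software to obtain thicknesses of each corneal sublayers" (section 3.4). UL-OCT gives corneal thickness (section 2.1).
- **Positions.** Section 3.3.2, part B, lists six two-dimensional UHR-OCT scans, for example "Nasal horizontal 2D scanning", and one radial scan.
- **Keratoconus.** Aim B reads "Observe the cornea images acquired from keratoconus patients in different stages" and then asks how thickness relates to stage.
- **Eyes.** One eye per subject is chosen from a random number table (section 3.3.2).

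**The concern.** Aim A is longitudinal: the same eye is measured before surgery and up to five times after it, and the hypothesis concerns change over time. The listed methods, taken as written, serve that aim poorly in three ways.

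1. A two-sample t-test at each visit asks whether the methods differ on that day. It does not ask whether the difference changes from 1 day to 3 months. Significance at one visit and not at another does not show that it does.
2. Each per-visit test uses only the eyes present that day. Section 4.4 lets subjects leave and rejoin, so successive tests may compare different sets of eyes.
3. Ordinary regression and Pearson's correlation assume independent observations. The quantities that section 1.3 wants to correlate can be measured at several visits. If all eye-visits enter one correlation, that assumption fails.

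At stake are the error rate behind a statement that flap methods differ or that oedema tracks regression, and the efficient use of visits already paid for.

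**Working it through.** **No figure to reproduce.** The protocol gives no alpha, sample size, standard deviation or within-eye correlation. What follows is illustration under assumptions: two-sided alpha 0.05, 30 eyes per flap method (30 eyes in all for the correlation), m = 5 post-operative visits, and equal correlation ρ between any two visits of one eye.

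**Step 1. A single test.** One eye per subject is scanned, so a comparison of methods at one visit has one value per subject and holds its nominal 5%. In simulation a paired t-test between two visits of the same eyes also holds about 5% at every ρ. These uses are sound.

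**Step 2. Five per-visit t-tests, one layer, one position.**
- Independent visits: 1 − 0.95^5 = 22.6%.
- Simulated with correlated visits: about 21% at ρ = 0.3, 18% at 0.5, 15% at 0.7 and 10% at 0.9.
- With only the four post-operative visits named in Aim A, the independent figure is 1 − 0.95^4 = 18.5%.

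Correlation between visits reduces the excess but does not remove it.

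**Step 3. Pearson's correlation on pooled eye-visits, no true association.** This applies only if visits are pooled. With both variables having intraclass correlation ρ, the variance of the pooled coefficient is inflated by about D = 1 + (m − 1)ρ². The type I error is about 2[1 − Φ(1.96/√D)].

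| ρ | D | Formula | Simulation |
|---|---|---|---|
| 0.3 | 1 + 4 × 0.09 = 1.36 | 9.3% | 9.2% |
| 0.5 | 1 + 4 × 0.25 = 2.00 | 16.6% | 16–17% |
| 0.7 | 1 + 4 × 0.49 = 2.96 | 25.5% | 25–26% |
| 0.9 | 1 + 4 × 0.81 = 4.24 | 34.1% | 34–35% |

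**Step 4. A flap-method t-test on pooled eye-visits.** Method is constant within an eye, so D = 1 + (m − 1)ρ. At ρ = 0.5, D = 3 and the error is 2[1 − Φ(1.96/√3)] = 25.8%, against 25.7% simulated. Again this applies only if visits are pooled.

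**Step 5. The direction is not always upward.** If two visits of the same eyes were compared by an unpaired t-test, the simulated type I error would be 2.1% at ρ = 0.3 and 0.7% at 0.5. That test is conservative and wastes power.

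**Step 6. Stage.** The number of stages is not given. If every pair of 3, 4 or 5 stages were compared by t-test with 30 eyes each, the simulated chance of at least one false positive would be 12.1%, 20.6% or 27.9%. A linear regression with one trend term for stage is a single test at 5%.

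**The case against.** The strongest reply is that section 3.6 is a bare list, and that a protocol may leave pairing, model form, covariance structure and multiplicity rules to an SAP. Much of this stands. The absence of those details is not a fault here. A reader might infer that the plan necessarily ignores within-eye correlation, but the text does not support that. A paired t-test accounts for the correlation between two visits, a single-visit comparison of methods does not need to, and a t-test on each eye's change between two visits would even test one method-by-time contrast. One-eye sampling also removes fellow-eye clustering. Pooling of eye-visits is nowhere stated.

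A reader might also multiply layers, positions and visits into one large grid of t-tests and count expected false positives. The protocol does not plan such a grid: total thickness belongs to UL-OCT, while the nasal, temporal, superior and inferior scans are UHR-OCT.

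Nor is the plan without a suitable tool for stage. Linear regression is listed and can take stage as a predictor, and nothing assigns t-tests or Pearson's correlation to Aim B. Section 1.3 is worded as exploration, and missed visits cost a per-visit test precision without by themselves making it invalid.

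What remains is that the protocol does name its methods, and the named set contains nothing that uses all six visits of an eye together. That is a mismatch between stated methods and stated aim, not merely missing detail.

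**Conclusion.** The point holds in a limited form. For a six-visit comparison of two flap methods, the listed methods do not, as listed, model repeated measures or test a difference in time course. Valid single-visit and paired tests are available within the list, but as a set they answer Aim A only piecemeal.

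The size depends on how the list is applied:
- Five per-visit tests of one layer at one position carry about a 10% to 23% chance of at least one false positive.
- Pearson's correlation on pooled eye-visits would have a type I error of roughly 16% to 35% over intraclass correlations of 0.5 to 0.9.

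The first range rests on an assumed alpha, group size and correlation. The second also needs visits to be treated as independent, which the text leaves open. For stage, the point is only to choose the right method from those already listed. The change is worth making because it affects the main comparison and is cheap.

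**What to change.** Reword section 3.6 as follows.

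- **Aim A.** Replace separate t-tests with one linear mixed model per layer using all visits: flap method, visit, method × visit, the pre-operative value where one exists (flap thickness has none), and an eye-level random effect or unstructured covariance. State whether the 3-month visit belongs to Aim A, since sections 1.2 and 3.3.2 differ.
- **Primary contrast.** Name one, such as central flap thickness between methods at one stated visit. Label the other layers, positions and visits as secondary.
- **Associations over visits.** Enter the predictor in the same mixed model; do not compute Pearson's correlation on pooled eye-visits. A correlation at one stated visit may stay.
- **Aim B.** Use the linear regression already listed, with stage as an ordered predictor and a trend contrast, or Spearman's correlation, in place of Pearson's correlation or pairwise t-tests.

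The cost is a few sentences and slightly more programming. No new data, visits or subjects are needed. The mixed model keeps eyes with missed visits, on the assumption that missingness depends only on what was observed.

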**4.1 Consent information**

This study was approved by the Office of Research Ethics, Wenzhou Medical University, Wenzhou, Zhejiang, China. Written consent form was obtained from each subject. Subjects were treated according to tenets of the Declaration of Helsinki. All subjects were recruited at the Refractive Surgery Division of the Affiliated Eye Hospital of Wenzhou Medical University.

Study was performed between 8:00 AM~5:00 PM. Totally no more than 0.5 hour.

**4.2 Treatment arragement**

If adverse effects happen during the study, all subjects will treated by ophthalmologist clinically.

**4.3 Adverse events**

Since this study is totally non-contact and non-invasive, the rate of adverse events was low. The possible adverse events were uncomfortable feeling caused by long time fixing and so on. All subjects will be treated by clinical ophthalmologist no matter the reasons for the uncomfortable. Relative doctors will get involved in the treatment when it necessary. Subjects can exit and quit the study when they are willing to. Adverse events might be kept as video records when necessary. Adverse events should be reported to the Office of Research Ethics and make detailed treatment plans.

**4.4 Casing study**According to tenets of the Declaration of Helsinki, subjects can exit the study anytime belonging to individual wishes. If the cooperation was not that good, study will be quited. All subjects will be treated by clinical ophthalmologist no matter the reasons for the uncomfortable. Subjects may rejoin the study when the issues were properly solved.

**5 Study records**

Each subject will be documented separately. Researcher should keep detailed and private information for each subject. The reports of each visiting will be maintained and concluded after each study time spot. Researcher should check the study results and sign the names and date with black pen formally. If the information need to be corrected, single horizontal line should be used to mark over the records and sign with the researcher’s name and date. The corrected part should be maintained recognizable. If the records are not able to be distinguish, “*” should be marked with commons. The OCT image results of each subject will be recorded in DVD discs and named after naming rules. The results may be used to compare with clinical results when necessary. All the records will be well kept at least 5 years.

**7 Attachments**

**7.1 Naming rules**

**7.1.1 UL-OCT naming rules:**

[figure not shown]

[figure not shown]

**7.1.2 UHR-OCT naming rules：**

[figure not shown]

**
[figure not shown]
**
